## Abstract

**Background:**

Gastrointestinal and psychological symptoms jointly motivate patients with irritable bowel syndrome (IBS) to seek medical care, with the latter often exacerbating the difficulty of achieving overall improvement. Although acupuncture has been shown to improve gastrointestinal symptoms in the general IBS population, the evidence in individuals with psychological disturbances remains insufficient.

**Methods:**

This will be a placebo run-in, randomized controlled trial. After the 1-week sham acupuncture intervention run-in period, the 80 eligible IBS patients without strong placebo responses will be randomly assigned to the true acupuncture (TA) group and sham acupuncture (SA) group. During the 4-week intervention period, all patients will receive the assigned intervention three times per week, followed by an 8-week follow-up. The primary endpoint is the response rate, defined as the proportion of patients with a decrease of greater than or equal to 50 points in the IBS Symptom Severity Scale (IBS-SSS) score from baseline at week 4. Secondary outcomes include the response rates at other time points, original IBS-SSS scores, Hospital Anxiety and Depression Scale (HADS), Visual Analog Scale (VAS) for abdominal pain, satisfaction with bowel habits, blinding assessment, and Credibility/Expectancy Questionnaire. Safety will be monitored and recorded during the trial.

**Discussion:**

This trial will provide individualized evidence for addressing IBS with key comorbidities while excluding placebo response. The results of this trial will be published in a peer-reviewed journal.

**Clinical Trial Registration:**

https://itmctr.ccebtcm.org.cn/mgt/project/view/1985616257155727360, identifier ITMCTR2025002100.

## Introduction

1

Irritable bowel syndrome (IBS) is a common disorder of gut-brain interaction characterized by abdominal pain associated with changes in stool form or bowel habits (1), affecting approximately 5–10% of the general population (2). Due to its recurrent and chronic nature, IBS significantly impairs quality of life and increases healthcare burden (3, 4). The annual direct and indirect costs of IBS are estimated to be about $10 billion across different countries and regions (5–7).

Beyond gastrointestinal symptoms, IBS is frequently associated with mental disorders (8). A recent meta-analysis revealed that the prevalence of anxiety and depression among patients with IBS was 39% and 29%, respectively, and that 23% of patients suffered from both conditions (9). Mental disorders in patients with IBS require increased attention, as they may aggravate disease severity and are associated with serious outcome such as disability or suicide (10). Current first-line pharmacological therapies, including laxatives, antidiarrhoeals, and antispasmodics, primarily target gastrointestinal symptoms and provide limited direct benefit for mental health (11). Due to safety concerns with long-term treatment, non-pharmacological approaches are receiving increasing attention.

Acupuncture has long been used as an option for the management of gastrointestinal symptoms (12), as well as primary psychological disorders (13, 14). Due to gut–brain interactions, patients with accompanying psychological symptoms may find it more difficult to achieve overall improvement. Our previous studies in the general IBS population have revealed that acupuncture is both safe and effective for alleviating gastrointestinal symptoms (15, 16). Although acupuncture appeared to improve mental health, no statistically significant difference was observed compared with the sham acupuncture. This unclear effect may be attributed to the mild baseline mental symptoms, and the absence of specific acupoints with sedative effects, both of which may have influenced outcomes. Therefore, to address the lack of evidence on this common comorbidity, the present study aims to evaluate the efficacy and safety of acupuncture in patients with IBS and coexisting mental health conditions.

## Methods and analysis

2

### Study design

2.1

This will be a randomized controlled clinical trial involving patients with IBS. Eligible patients will be randomly allocated to the true acupuncture group (TA) or the sham acupuncture group (SA) in a 1:1 ratio. The 13-week study consists of a 1-week placebo run-in period, a 4-week treatment period and an 8-week follow-up. The study protocol was approved by the Medical Ethics Committee of Xiyuan Hospital, China Academy of Chinese Medical Sciences (Approval ID: 2025XLW019-1), and was registered (International Traditional Medicine Clinical Trial Registry: ITMCTR2025002100). The present trial will be performed following SPIRIT 2025 statement (Additional file 1). **Figure 1** shows the study flowchart. All personnel involved in this trial will receive standardized training on the trial procedures.

**Figure 1 f1:**
[figure not shown]
Study flowchart. IBS, irritable bowel syndrome.

### Participants

2.2

#### Diagnostic criteria

2.2.1

According to the 2016 Rome IV diagnostic criteria (17), IBS is diagnosed by the presence of recurrent abdominal pain, on average at least one day per week in the last three months, accompanied by two or more of the following criteria:

Related to defecation;Associated with a change in frequency of stool;Associated with a change in form (appearance) of stool.

Criteria fulfilled for the last 3 months with symptom onset at least 6 months before diagnosis.

#### Inclusion criteria

2.2.2

Individuals aged between 18 and 75, irrespective of gender;Participants fulfill the diagnostic criteria of Rome IV for irritable bowel syndrome;The Irritable Bowel Syndrome Symptom Severity Scale (IBS-SSS) scores ≥75 points, and the Hospital Anxiety and Depression Scale (HADS) scores ≥11 points;No suicidal behavior within the past 3 months and the Suicidal Behaviors Questionnaire-Revised (SBQ-R) scores <7;Prospective participants do not have undergone acupuncture treatment for irritable bowel syndrome or taken psychiatric medications within the preceding six months;Should a participant be on medications that alleviate irritable bowel syndrome symptoms, such as traditional Chinese medicine, Chinese patent medicine, antidiarrheal drugs, antispasmodics, intestinal antibiotics, or probiotic preparations, prior to the commencement of treatment, they must discontinue use at least two weeks prior to the onset of treatment.

#### Exclusion criteria

2.2.3

History of organic intestinal disorders, including inflammatory bowel disease, microscopic colitis, celiac disease, or Crohn’s disease;Diabetes mellitus and thyroid dysfunctions;Severe acute or chronic organic diseases, kidney or liver diseases;History of abdominal surgeries (including appendectomy, hemorrhoidectomy, and polypectomy conducted more than three months prior);Pregnancy or lactation;History of alcohol or drug misuse;Patients currently participating in other clinical trials.

### Recruitment and informed consent

2.3

Patients will be recruited at the Acupuncture Hospital of the China Academy of Chinese Medical Sciences through print or online advertisements, including newspapers, websites, and hospital posters. Prior to formal participation, the investigator shall inform the patient of the trial’s background, study procedures, and the study’s significance. Comprehensive information regarding the potential benefits, risks, and discomforts associated with participating in the study will be furnished to guarantee that the patient thoroughly understands the study. Patients will decide whether or not to participate in the trial and may withdraw at any time during the trial. For those patients who refuse to participate in this trial, they will be advised of other conventional treatments if requested. All relevant personal information about the patient, which may include occupation, medical history, condition, physical examination and laboratory results, will be kept confidential.

In addition to the detailed informed notification process, the following efforts will be made to ensure patient adherence: First, the scientific background of the research team and recent advances in disease research will be introduced. Second, the operation, clinical efficacy, safety, and possible mechanisms of acupuncture will be explained. Third, patients who complete the trial will receive an additional free acupuncture treatment at the end of the study.

### Run-in period

2.4

Eligible patients will first undergo a one-week placebo run-in period, designed to identify those with a strong placebo response and exclude them prior to randomization. This approach allows for a more accurate assessment of the net effect of the intervention and enables participants with poor compliance to voluntarily withdraw before randomization (18, 19). For acupuncture, excluding strong placebo responders facilitates a clearer evaluation of its specific effects, ensuring that observed improvements in gastrointestinal and psychological symptoms can be more confidently attributed to the intervention rather than placebo responses. After run-in baseline assessments, all patients will receive a single-blind sham acupuncture intervention three times per week for one week, following the same procedure as the SA group. Patients who achieve a reduction of ≥50 points on the IBS-SSS during this period will be considered placebo responders and excluded from randomization.

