### Randomization and allocation concealment

2.5

Patients who are not excluded after the run-in period will undergo treatment baseline assessments and be randomly assigned in a 1:1 ratio to the TA or SA group. An independent statistician, not involved in the trial’s implementation or statistical analysis, will generate the randomization sequence using SAS 9.3 software. Sequentially numbered, opaque, sealed envelopes will be used to implement the random allocation. Recruiters will register participants, while acupuncturists will assign the interventions.

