#### Primary outcome

2.7.1

The primary outcome will be the response rate, defined as the proportion of patients achieving a reduction of ≥50 points in the IBS-SSS (20) from baseline, which is recommended by the U.S. Food and Drug Administration (21). The primary endpoint will be the between-group comparison of response rate at week 4. The IBS-SSS consists of five items rated on a visual analog scale (0–100): severity of abdominal pain, frequency of abdominal pain, severity of abdominal distension, dissatisfaction with bowel habits, and interference with quality of life. Each item contributes equally to the total score, with an overall range of 0–500.

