#### Secondary outcomes

2.7.2

Original IBS-SSS scores will be assessed as secondary outcomes at baseline and at weeks 2, 4, 8, and 12. The response rate will also be evaluated as a secondary outcome at baseline and at weeks 2, 8, and 12.

Hospital Anxiety and Depression Scale (HADS) (22). Symptoms of anxiety and depression will be assessed using the HADS at baseline and at week 2, 4, 8, and 12. The HADS is a validated 14-item instrument comprising two subscales for anxiety and depression. Scores are interpreted as follows: 0–7, no symptoms; 8–10, suspected symptoms; and 11–21, definite symptoms (23).

Visual Analog Scale (VAS) (24). The worst abdominal pain over the preceding 24 hours will be evaluated by VAS (0–10), with 0 indicating no pain and 10 indicating the worst imaginable pain. VAS will be evaluated at baseline and at week 2, 4, 8, and 12.

Satisfaction with bowel habits (25). Patients’ satisfaction with defecation will be assessed using a 7-point Likert scale, with response options ranging from “strongly disagree” to “strongly agree.” This scale provides an appropriate balance between sensitivity and usability, allowing for more nuanced assessment than a five-point scale while avoiding the cognitive burden of scales with more response options. Assessments will be conducted at baseline and at week 2, 4, 8, and 12.

Credibility/Expectancy Questionnaire (26). The credibility and expectancy to the intervention will be measured within 5 minutes after the first intervention session completed.

Blinding. The blinding assessment will be conducted by asking participants to guess their intervention allocation at week 2 and 4.

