#### Sample size

2.10

There is a lack of direct evidence on acupuncture for patients with IBS comorbid with anxiety and depression. The response rate for the SA group was derived from studies in general IBS populations because sham effects are expected to be minimal and not substantially influenced by comorbid anxiety or depression, and based on our previous study it was approximately 25% (15). For the TA group, both the established effects of acupuncture in general IBS populations and evidence from large-scale meta-analysis showing moderate-to-large effect size (Cohen’s d = 0.66) of acupuncture for depression were taken into account (13). Considering the potential secondary improvement in gastrointestinal symptoms via acupuncture targeting anxiolytic and sedative acupoints, we estimated a response rate of approximately 60% in the TA group by the end of the week 4. With α = 0.05, 36 participants per group are required to achieve 80% power. Accounting for a 10% dropout rate, a total of 80 participants will be recruited.

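### The run-in is credited with making psychological improvements attributable to acupuncture, but it screens only on the IBS-SSS, so the added assurance for the HADS is not ensured

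*Protocol article*

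**What the plan says.** Section 2.4 (Run-in period) gives the purpose of the sham week as identifying strong placebo responders and excluding them, "ensuring that observed improvements in gastrointestinal and psychological symptoms can be more confidently attributed to the intervention rather than placebo responses". The rule that carries this out is in the same section: "Patients who achieve a reduction of ≥50 points on the IBS-SSS during this period will be considered placebo responders and excluded from randomization". No other measure enters it.

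Section 2.5 then takes everyone else forward: "Patients who are not excluded after the run-in period will undergo treatment baseline assessments and be randomly assigned in a 1:1 ratio".

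Section 2.7.1 lists the five IBS-SSS items as "severity of abdominal pain, frequency of abdominal pain, severity of abdominal distension, dissatisfaction with bowel habits, and interference with quality of life". None of them is an anxiety or depression item. Psychological symptoms have their own scale in section 2.7.2: "Symptoms of anxiety and depression will be assessed using the HADS at baseline and at week 2, 4, 8, and 12". The HADS is also an entry condition in section 2.2.2 ("the Hospital Anxiety and Depression Scale (HADS) scores ≥11 points"), but it is not used again as a condition after the run-in.

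Section 2.11 compares continuous secondary endpoints between groups by t test or Wilcoxon rank sum test, without adjustment for baseline.

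**The concern.** The rationale names two symptom domains and the rule acts on one. A patient whose anxiety or depression score drops markedly under sham needling, but whose IBS-SSS falls by less than 50 points, is randomised. A patient with no HADS change and an IBS-SSS fall of 50 points is removed. For the HADS, the filter works on a different quantity from the one in the claim.

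This matters because psychological comorbidity is the reason for the trial. The Introduction says that the team's studies in general IBS found no significant mental-health difference from sham, and presents this trial as the response. Two acupoints are included for negative emotions. The abstract's discussion speaks of excluding placebo response without limiting this to bowel symptoms. The main Discussion says the IBS-SSS responder definition also helps to evaluate psychological status, which the item list does not bear out beyond a general quality-of-life item. A reader could therefore carry the run-in's assurance over to the HADS result. At stake is how firmly a secondary mental-health conclusion is worded.

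**Working it through.** **1. The plan's own figure.** The sample size rests on the IBS-SSS response rate alone. Sham is put at 25% ("based on our previous study it was approximately 25" per cent), and for true acupuncture "we estimated a response rate of approximately 60% in the TA group". With two-sided α = 0.05 and 80% power:

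- Uncorrected: n = [1.960·√(2·0.425·0.575) + 0.842·√(0.25·0.75 + 0.60·0.40)]² / 0.35² = 30.1.
- Continuity-corrected: n′ = (30.1/4)·[1 + √(1 + 4/(30.1·0.35))]² = 35.6, so 36 per group.
- Dropout: 36/0.90 = 40 per group, 80 in total.

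The stated 36 and 80 reproduce. Nothing in this point changes them.

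**2. Claim against rule.** The claim covers gastrointestinal and psychological symptoms. The screen is an IBS-SSS fall of at least 50 points. All patients not so excluded are randomised. HADS run-in responders are removed only where they are also IBS-SSS run-in responders.

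**3. How many could remain (illustration).** The documents give no HADS run-in response rate, no one-week IBS-SSS sham response rate and no correlation between the two changes. Assume that a proportion pI respond on the IBS-SSS, that pH = 25% have a marked HADS fall, and that the two changes are bivariate normal with correlation r. Let J be the probability of responding on both.

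- Share of HADS responders retained = (pH − J)/pH.
- Their share of the randomised = (pH − J)/(1 − pI).

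At r = 0 and pI = 25%, J = 0.25 × 0.25 = 0.0625, so retained = 0.1875/0.25 = 75% and share of randomised = 0.1875/0.75 = 25%.

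| r (pI = 25%) | HADS responders retained | Share of randomised | Of 80 |
|---|---|---|---|
| 0 | 75% | 25% | 20 |
| 0.3 | 62% | 21% | 17 |
| 0.5 | 52% | 17% | 14 |
| 0.7 | 40% | 13% | 11 |

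With no run-in the share would be 25%. Varying pI from 15% to 35% and r from 0 to 0.7, retention runs from 85% (pI = 15%, r = 0) to 26% (pI = 35%, r = 0.7). The rule thus gives nothing for the HADS at r = 0 and a partial, indirect reduction at any positive r.

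**4. What adjustment would gain (illustration).** Assume HADS at entry (E), treatment baseline (B) and week 4 (Y) with equal variance σ² and common correlation ρ.

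- Unadjusted change Y − B has variance 2(1 − ρ)σ².
- Its covariance with the run-in change B − E is −(1 − ρ)σ², and B − E also has variance 2(1 − ρ)σ². The squared correlation is therefore (1/2)² = 0.25: adding the run-in change cuts the residual variance of the change score by 25% at any ρ.
- With both B and B − E in the model, the residual variance is [1 − 2ρ²/(1 + ρ)]σ². At ρ = 0.4 this is 0.771 against 1.2, a 36% cut. At ρ = 0.7 it is 0.424 against 0.6, a 29% cut.

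**The case against.** The strongest reply is that the sentence in section 2.4 is comparative. It speaks of more confident attribution and does not promise a population cleared of psychological placebo responders. The protocol's premise is that gut and mood are linked, so a positive correlation is plausible, and the illustration then shows some benefit for the HADS: 25% falls to 21%, 17% or 13%. The rule is also stated openly in the same section. All of this stands. It is why the point is that the property is not ensured, rather than that it is absent.

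A reader might go further and infer that the HADS comparison is biased or cannot support a conclusion about mental health. The documents do not support that. Allocation is randomised 1:1, patients and outcome assessors are blinded, the control is sham needling of the same duration, and section 2.11 plans between-group comparisons. HADS placebo responders who remain are balanced between arms in expectation. That a HADS fall within one arm may be placebo response is true of any sham-controlled trial, and it is not the inference planned here.

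The sizes in the table rest wholly on assumed inputs and say nothing about the between-group HADS estimate. They show that removal may be far from complete, not how far it is. It can also be said that the covariate is a matter for an analysis plan. However, section 2.11 does name unadjusted tests, so a better choice can fairly be suggested. The wording correction does not depend on it.

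**Conclusion.** The point holds in limited form. The run-in screens directly on IBS-SSS response only. Any screening of psychological placebo response is a by-product, of a size that the documents do not allow anyone to state. Under the assumptions above (25% responders on each scale, bivariate normal changes, correlation 0 to 0.7), 40% to 75% of HADS run-in responders would be randomised. Varying the IBS-SSS run-in rate from 15% to 35% widens this to 26% to 85%.

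The consequence lies in interpretation: the run-in cannot be cited as added assurance for a HADS result. The validity of the HADS comparison rests on randomisation, blinding and the sham control, and is unaffected. The HADS is a secondary outcome, and the primary endpoint and the 80 patients stand. This is a modest correction worth making before the results are interpreted.

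**What to change.** - **Section 2.4:** limit the attribution sentence to IBS-SSS outcomes and state that psychological placebo response is not directly screened. Keep the exclusion rule as it is.
- **Section 2.11:** replace the unadjusted t or Wilcoxon test for the HADS with a model of the week-4 score (and likewise at other visits) on treatment group and pre-randomisation HADS. Use the treatment-baseline score taken after the run-in, plus the change from entry to treatment baseline where both are recorded.
- **Section 2.7.2:** say that the HADS baseline is the treatment baseline. The text says only baseline, while sections 2.4 and 2.5 describe two baseline assessments.
- **Reporting:** give the HADS change over the run-in. Because entry requires a score of at least 11, part of any fall may be regression to the mean, so it should not be labelled as placebo response alone.

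The cost is a few sentences, one or two covariates and a little more analysis work. No extra patients are needed, and no extra visits if the HADS is recorded at both entry and treatment baseline. The protocol implies this but does not state it outright. If only the treatment-baseline score exists, adjust for that alone. The gain is precision and a correctly limited conclusion. It does not remove a bias, because there is none to remove, and it does not supply a psychological screen.

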### Randomization and allocation concealment

2.5

Patients who are not excluded after the run-in period will undergo treatment baseline assessments and be randomly assigned in a 1:1 ratio to the TA or SA group. An independent statistician, not involved in the trial’s implementation or statistical analysis, will generate the randomization sequence using SAS 9.3 software. Sequentially numbered, opaque, sealed envelopes will be used to implement the random allocation. Recruiters will register participants, while acupuncturists will assign the interventions.

#### Blinding

2.5.1

Due to the characteristics of acupuncture treatment process, only the acupuncturist and their assistant will have access to the randomization information. Patients, clinical recruiters, outcome assessors, data managers, and statisticians will be blinded to the group allocation. Unblinding of the study data will occur after the database has been locked and all participants have completed the trial.

Permitted circumstances for unblinding include (1): when a patient experiences a serious adverse event necessitating knowledge of the assigned intervention for clinical management (2); when the trial protocol contains major design flaws that threaten the scientific integrity of the results or constitute a hazard to participant rights and safety; and (3) legal requirements. If unblinding is necessary, the principal investigator will be immediately notified, and an assessment panel will evaluate the need for unblinding. If it is deemed necessary, the custodian responsible for safeguarding the randomization information will release the details according to established protocols, with the unblinding process carefully documented. The ethics committee will be informed upon completion of the unblinding.

